# The synergistic effect of acupuncture and computer-based cognitive training on post-stroke cognitive dysfunction: a study protocol for a randomized controlled trial of 2 × 2 factorial design

**DOI:** 10.1186/1472-6882-14-290

**Published:** 2014-08-07

**Keywords:** Acupuncture, Computer-based cognitive training, Stroke, Cognitive dysfunction

## Abstract

**Background:**

Stroke is one of the most common causes of cognitive impairment. Up to 75% of stroke survivors may be considered to have cognitive impairment, which severely limit individual autonomy for successful reintegration into family, work and social life. The clinical efficacy of acupuncture with Baihui (DU20) and Shenting (DU24) in stroke and post-stroke cognitive impairment has been previously demonstrated. Computer-assisted cognitive training is part of conventional cognitive rehabilitation and has also shown to be effective in improvement of cognitive function of affected patients. However, the cognitive impairment after stroke is so complexity that one single treatment cannot resolve effectively. Besides, the effects of acupuncture and RehaCom cognitive training have not been systematically compared, nor has the possibility of a synergistic effect of combination of the two therapeutic modalities been evaluated. Our primary aim of this trial is to evaluate the synergistic effect of acupuncture and RehaCom cognitive training on cognitive dysfunction after stroke.

**Method/Design:**

A randomized controlled trial of 2 × 2 factorial design will be conducted in the Rehabilitation Hospital Affiliated to Fujian University of Traditional Chinese Medicine. A total of 240 patients with cognitive dysfunction after stroke who meet the eligibility criteria will be recruited and randomized into RehaCom training group, acupuncture group, a combination of both or control group in a 1:1:1:1 ratio. All patients will receive conventional treatment. The interventions will last for 12 weeks (30 min per day, Monday to Friday every week). Evaluations will be conducted by blinded assessors at baseline and again at 4, 8 and 12 weeks. Outcome measurements include mini–mental state examination (MMSE), Montreal cognitive assessments (MoCA), functional independence measure scale (FIM) and adverse events.

**Discussion:**

The results of this trial are expected to clarify the synergistic effect of acupuncture and RehaCom cognitive training on cognitive dysfunction after stroke. Furthermore, to confirm whether combined or alone of acupuncture and RehaCom cognitive training, is more effective than conventional treatment in the management of post-stroke cognitive dysfunction.

**Trial registration:**

Chinese Clinical Trial Registry: ChiCTR-TRC-13003704.

Registration date: 4 September, 2013.

## Background

Stroke is the leading cause of death worldwide [1]. Perhaps more importantly, those who survive stroke have various neurologic deficits, including physical and motor skill impairment and serious psychological consequences. The latter may affect cognition, impairing processes such as attention and concentration, memory, planning, calculations and language as well as emotions and behaviors [2, 3]. Cognitive impairment is one of the most common disorders caused by stroke [4–7]. Approximately 25% of patients present with cognitive impairment 3 months after a stroke. Furthermore, up to 75% of stroke survivors may be considered to have cognitive impairment [8–10]. After stroke, the risk of developing dementia doubles, and the progression rate from mild cognitive impairment to dementia increases [11, 12]. Cognitive impairment after stroke is, therefore, an unfortunately common problem and will likely become more of one as people live longer [13].

Despite a high prevalence of post-stroke cognitive impairment, therapeutic possibilities are still limited. Several life style interventions [such as smoking cessation, moderation of alcohol intake, healthy diet (e.g., Mediterranean diet), weight control and physical activity] have been used in clinical practice,which potentially can help to prevent progression or occurrence of vascular cognitive impairment. Nonetheless, there are still no FDA-approved treatments for cognitive impairment after stroke [14]. By and large, drug trials have failed to show improvement in global cognitive functioning, activities of daily living, and quality of life [14]. Treatment options for cognitive impairment after stroke remain limited and poorly supported [13].

As a result, complementary or alternative therapies, such as acupuncture, are attractive to both patients and practitioners. Acupuncture, a core component of Traditional Chinese Medicine (TCM), has been used for thousands of years in several oriental countries to treat various diseases, with virtually no side effects in competent hands. A number of studies [15–21] demonstrated that acupuncture techniques may be effective for improving intelligence, stimulating consciousness and enhancing memory. These effects may result from activation and/or stimulation by acupuncture of the regions responsible for cognition. In the system of TCM, Baihui (DU 20) and Shenting (DU24) are acupoints that belong to the Du Meridian and may be important in the nervous system. Acupoint Shenting (DU24) is considered to be involved in the improvement of human health and spirits, and Baihui (DU20) in the adjustment of memory function. Therefore, the Baihui and Shenting acupoints are commonly used in China to clinically treat post-stroke cognitive impairment [22, 23]. A series of experimental studies have demonstrated that acupuncture can improve cognitive function through: 1. regulating the aging related changes in gene profile expression of the hippocampus [24]; 2. preventing oxidative stress [25]; 3.regulating the expression of apoptosis related genes in hippocampus [26, 27].

Cognitive rehabilitation (CR) is a mechanism that can compensate for an impaired nervous system by systematic treatment that can cause functional changes through the reinforcement, promotion and relearning of previously learned or new patterns to enhance cognitive function [28]. At present, cognitive training mainly includes traditional cognitive retraining and computer-assisted cognitive training, e.g. [29]. Computer-assisted cognitive training allows automation of many cognitive training procedures, making it possible to meet demand for care, improve stimulation quality, increase patient record reliability and optimize performance in impaired functions [30, 31].

RehaCom is one of the most widely used computer-assisted cognitive training software packages, enabling focus on various cognitive areas that need to be trained [32], which has shown excellent results in clinical practice with no major negative effects reported [33]. To date, the RehaCom system has been widely used in relevant diseases rehabilitation [34, 35]. The RehaCom system promises a series of advantages over traditional cognitive training, on the basis of pen-and-paper exercises. The RehaCom program has sufficient flexibility, simplicity, accessibility, dynamics and objectivity to make a useful contribution to clinical practice. Its interactive capabilities and multimedia make it possible to keep patients motivated, irrespective of multiple motor and sensory deficits. Its use enables more precise recording of patient results and increased quality of stimulation. It also allows setting the initial level of task difficulty according to the individual’s baseline competency and gradually increasing it as patients improve their performance, resulting in a continuous cognitive challenge. In addition, RehaCom enables the standardization of intervention [33].

As mentioned above, the acupuncture focus on the global cognitive function from the holistic conception of TCM, while the RehaCom cognitive training concerns the specific impaired cognitive functions which need to be trained from the viewpoint of symptomatic treatment. However, the cognitive impairment after stroke is so complexity that one single treatment cannot resolve effectively. Due to the limited efficacy of the interventions separately used and the growing interest in recovery from post-stroke cognitive dysfunction has led to development of multiple therapeutic strategies for cognitive rehabilitation, that is, the remediation or alleviation of cognitive deficits resulting from neurological damage [36]. As the two interventions which can treat the cognitive impairment from global cognitive function to specific impaired cognitive function, we firmly believe that the interaction of multiple therapeutic strategies (the combination of acupuncture and RehaCom cognitive training) to produce an effect greater than simply the sum of the individual effects of each intervention if they were used separately. Besides, the effects of acupuncture and RehaCom cognitive training have not been systematically compared, nor has the possibility of a synergistic effect of combination of the two therapeutic modalities been evaluated.

Nonetheless, after reviewing a great amount of literature, we found that few studies had addressed these questions. So it is still unclear whether this form of intervention (acupuncture combined with RehaCom cognitive training) can be considered as a treatment of choice. Though, a current systematic review [37] showed that acupuncture in combination with other therapies could significantly improve cognitive functions. Besides, acupuncture would be a useful tool in conjunction with RehaCom from our preliminary clinical practice. However, convincing evidence is still inadequate. Therefore, we designed a randomized controlled trial of 2 × 2 factorial design to address these problems and hopefully provide a more conclusive answer to the questions. We hypothesized that the synergistic effect of acupuncture and RehaCom cognitive training is greater than simply the sum of the individual effects of each intervention if they were used separately; and the acupuncture or RehaCom cognitive training significantly improves cognitive outcomes, or to a similar extent, assessed after the intervention, compared to the control group.

In this trial, our first aim is to evaluate the synergistic effect of acupuncture and RehaCom cognitive training on cognitive dysfunction after stroke. Our second aim is to determine whether acupuncture and RehaCom cognitive training, alone or in combination, are more effective than conventional treatment on the rehabilitation of post-stroke cognitive dysfunction. The work reported in this article is financed by the Program of International S&T Cooperation (No. 2011DFG33240), Ministry of Science and Technology of the People’s Republic of China.

## Method/Design

### Study design and setting

We propose a randomized controlled trial with 2 × 2 factorial design in which the two interventions (acupuncture and RehaCom training) are to be delivered to **four** groups defined by the presence or absence of each intervention, with one arm without both interventions as a control group. Patients were randomized to one of the four treatment arms: (i) Experimental Group1 (EG1): conventional treatment plus RehaCom cognitive training; (ii) Experimental Group 2 (EG2): conventional treatment plus acupuncture treatment; (iii) Experimental Group 3 (EG3): conventional treatment plus the combination of acupuncture and RehaCom cognitive training; and (iv) Control Group (CG): Conventional treatment alone. All groups receive the same intervention time of 30 minutes. The investigation will have an intervention period of 12 weeks and will be carried out in the Rehabilitation Hospital Affiliated to Fujian University of Traditional Chinese Medicine (FJTCM). Cognitive abilities screening instrument on cognition performance [includes mini-mental state examination (MMSE), Montreal cognitive assessment (MoCA), functional independence measure scale (FIM)] will be assessed in all groups before and after randomization (at 0,4,8 and 12 weeks). The flow diagram for this trial is presented in Figure 1.

**Figure 1 Fig1:**
[figure not shown]
**Flow diagram of participants.**

### Sample size

We use the improvement of MMSE scores as the main effect indicators to estimate the sample size. Sample size calculations are performed to determine the number of participants needed to detect effect sizes. Based on the similar papers reported before [38–40] and our preliminary data indicates the mean with SD of the MMSE scores were μ1 = 2.7, μ2 = 5.9, μ3 = 3.7, μ4 = 6 in the CG, EG1, EG2, EG3 respectively, with the SD *σ* = 5.2. To detect 4.6 mean differences among the groups at end of interventions, k represents of the number of groups which is 4 in this trial. About 50 individuals per group will be calculated according to the formula:

With a type I error of 5% (α = 0.05) and 90% power (β = 0.10). Estimating a 20% dropout rate during the study, a minimum of 240 total participants is needed to reach the target 60 participants per group.

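### The sample-size section gives no power for the synergy contrast, and its own planning means imply a sub-additive interaction of -0.9 with about 9% power

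*Protocol article*

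**What the plan says.** The Background of the protocol article states that "our first aim is to evaluate the synergistic effect of acupuncture and RehaCom cognitive training on cognitive dysfunction after stroke". The hypothesis there is that the joint effect will be "greater than simply the sum of the individual effects of each intervention if they were used separately". The Abstract and the Discussion repeat synergy as the main purpose.

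The Sample size section sizes the trial on MMSE: "We use the improvement of MMSE scores as the main effect indicators to estimate the sample size". The assumed values are "μ1 = 2.7, μ2 = 5.9, μ3 = 3.7, μ4 = 6 in the CG, EG1, EG2, EG3 respectively", with a common SD of 5.2. CG is control, EG1 RehaCom, EG2 acupuncture and EG3 both. It continues: "To detect 4.6 mean differences among the groups at end of interventions", and "k represents of the number of groups which is 4 in this trial". From these it derives about 50 per group at a 5% type I error and 90% power, then 60 per group (240 in total) after allowing for 20% dropout. The section mentions neither an interaction effect nor power for an interaction test.

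The Statistical analysis section names ANOVA or Kruskal-Wallis at a two-sided 0.05 level. It mentions interactions only to say that significant ones will be followed up post hoc.

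**The concern.** In a 2 × 2 factorial trial, an effect beyond the sum of the parts is one contrast: EG3 - EG1 - EG2 + CG greater than zero. An omnibus comparison of four means answers a different question, namely whether any of the means differ. If the 90% belongs to the omnibus test, the only power figure in the article does not cover the first aim.

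Two misreadings follow. A non-significant interaction could be taken to show that there is no synergy, although the trial may have been unable to detect a moderate one. A significant omnibus test could be taken as support for synergy, although it may reflect one intervention working alone. In addition, planning means that run against the hypothesis leave the reader unsure what the investigators expected.

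**Working it through.** **Inputs.** All come from the Sample size section unless noted: means CG 2.7, EG1 5.9, EG2 3.7, EG3 6.0; SD 5.2; k = 4; alpha 0.05, two-sided (Statistical analysis section); power 0.90; 50 evaluable per arm. Assumption: 5.2 is the SD of MMSE improvement, with no baseline adjustment.

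**1. Reproduce the plan's figure.**
- Grand mean = (2.7 + 5.9 + 3.7 + 6.0)/4 = 4.575.
- Sum of squared deviations = 3.5156 + 1.7556 + 0.7656 + 2.0306 = 8.0675.
- Omnibus F test on 3 and 4(n - 1) df, noncentrality n × 8.0675/5.2². At n = 50 this is 14.92.
- Power: 89.7% at 48 per arm, 90.3% at 49, 91.0% at 50. So 49 per arm suffice for 90%, which matches about 50.
- Two-group alternatives at 90% power: a difference of 4.6 needs 27 per arm (40 with Bonferroni for six pairs). A difference of 3.3 needs 53, which is near the stated figure but uses neither k = 4 nor all four means.

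**2. The synergy contrast under the same means.**
- RehaCom alone: 5.9 - 2.7 = 3.2. Acupuncture alone: 3.7 - 2.7 = 1.0. Sum: 4.2.
- Combination: 6.0 - 2.7 = 3.3.
- Interaction = 3.3 - 4.2 = -0.9, which is sub-additive. Exchanging the EG1 and EG2 labels leaves it unchanged.

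**3. Power for that contrast at 50 per arm.**
- SE = 5.2 × √(4/50) = 1.471; standardised effect -0.9/1.471 = -0.61; 196 df.
- Two-sided power 9.3%: 8.8% towards antagonism and 0.5% towards synergy. A simulation of 200,000 trials gave 9.3%.
- With all 60 per arm retained: 10.2%, of which 0.4% towards synergy.
- Detectable with 90% power: (1.960 + 1.282) × 1.471 = 4.8 points; with 80% power, 4.1. The largest difference between any two planning means is 3.3.
- 95% CI half-width: 1.972 × 1.471 = 2.9 points.
- If the true synergy were +2 points, power would be 27%; if +3 points, 53%.

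**4. What drives the omnibus test.**
- RehaCom main effect: (3.2 + 2.3)/2 = 2.75, contributing 2.75² = 7.5625 to the sum of squares.
- Acupuncture main effect: (1.0 + 0.1)/2 = 0.55, contributing 0.55² = 0.3025.
- Interaction: 0.9²/4 = 0.2025.
- Total 8.0675, so RehaCom accounts for 7.5625/8.0675 = 93.7%.
- Power at 50 per arm (main-effect SE 0.735): RehaCom 96%, acupuncture about 12%.

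**5. The 4.6.** The six pairwise differences are 3.2, 1.0, 3.3, 2.2, 0.1 and 2.3. None is 4.6. The figure is close to the grand mean, 4.575.

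**The case against.** **The formula is missing from the text.** This stands. The omnibus basis is an inference from k = 4, the four means and the match of 49 to about 50. The 4.6, read as an interaction, would have 87.5% power at 50 per arm. Nothing in the section presents it as an interaction, though, and it contradicts the -0.9 from the listed means. The low power for -0.9 does not depend on which formula was used.

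**The article never claims 90% power for synergy.** A reader might infer that it does, since synergy is the first aim and only one power figure is given. The text ties the 90% to differences among four groups, so a charge of claiming it for synergy would go too far. What holds is that the first aim has no stated power.

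**Factorial trials are commonly powered for main effects.** That is sound when main effects are primary. Here the interaction comes first.

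**Baseline adjustment would help.** It would narrow the interval. If it removed half the variance (an assumption), the SE would be 1.04 and power for 0.9 about 14%. The sign would not change.

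**If the truth is -0.9, reporting no synergy is not wrong.** Correct. The risk of misreading lies with a real positive interaction below about 4 to 5 points. Nor is a non-significant interaction always uninformative: an estimate of -0.9 would have an upper limit of -0.9 + 2.9 = +2.0, which argues against larger synergy.

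**A full protocol or SAP may say more.** It may, but the means, the power and the hypothesis all stand in this article, and they do not agree.

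**Conclusion.** The point holds as a mismatch within the article. Its first aim and hypothesis are a super-additive interaction. Its sample-size section gives no power for that contrast, and its planning means imply -0.9 points. With 50 per arm, an SD of improvement of 5.2, no baseline adjustment and a two-sided 0.05 level, power is about 9% (about 0.5% in the hypothesised direction), and 90% power is reached only for an interaction of about 4.8 points. The sign of the interaction rests on the listed means alone; the power, detectable size and interval width rest on the SD and adjustment assumptions. That the 90% is an omnibus figure is the best reading, not a certainty.

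A significant omnibus result would not be evidence of synergy, since about 94% of the planned between-arm variation is the RehaCom main effect. The documents do not support saying that the trial can learn nothing about synergy: an interval of about ±2.9 points can still exclude large effects.

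**What to change.** Revise the sample-size and interpretation text:

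1. State that the 90% refers to the omnibus four-group comparison of the listed means (or, if another formula was used, which one). Remove or reconcile the 4.6.
2. State EG3 - EG1 - EG2 + CG as the estimand for the first aim. Give its detectable size (about 4.8 points at 90% power, 50 per arm) and its expected 95% CI half-width (about 2.9 points), noting that baseline adjustment may narrow both.
3. Acknowledge that the planning means are sub-additive and give under 10% power for the interaction at 50 per arm. Do not fit new means to the hypothesis; the article says these come from earlier papers and preliminary data.
4. Report the interaction as an estimate with its 95% CI and draw the conclusion from the interval. Neither a non-significant interaction alone nor a significant omnibus test should settle the question of synergy.

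The cost is wording and a less favourable stated power for the first aim. No patients are added and no treatment changes. Recruitment was ongoing at publication, so the change should be made before the allocation code is broken.

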### Participant and recruitment

We will recruit 240 eligible patients from the Rehabilitation Hospital Affiliated to FJTCM who suffer from cognitive disorders caused by stroke with age above 18 years. The eligible patients must meet the following inclusion criteria as well as the exclusion criteria. A CONSORT diagram of participant recruitment is shown in Table 1. Patients will be recruited as inpatients or from the outpatient therapy department of the rehabilitation hospital by their treating therapist, through an advertisement at the hospital’s homepage, and through flyers at several locations of the hospital. Interested patients can contact the project leader (PL) through their therapist, by phone, email, or mail. If an applicant meets the study criteria, he or she will be invited to the research.

**Table 1 Tab1:** **Trial processes chart**

Items	Before enrollment	Intervention period 1	Outcome assessment 1	Intervention period 2	Outcome assessment 2	Intervention period 3	Outcome assessment 3
	-2-1(week)	1-4(week)	5(week)	5-8(week)	9(week)	9-12(week)	13(week)
Inclusion criteria	×						
Exclusion criteria	×						
Informed consent	×						
Baseline	×						
Randomization and allocation	×						
Intervention		×		×		×	
Mini-mental status examination	×		×		×		×
Montreal cognitive assessment	×		×		×		×
Functional independence measure scale	×		×		×		×
Adverse events		×		×		×	
Reasons of drop-out and withdrawals		×		×		×	

### Inclusion criteria

For inclusion, patients (age between 18 and 75 years old) within six months after first-ever stroke (according to the criteria of ‘Diagnostic Criteria for All Kinds of Cerebrovascular Disease’ [41]) with cognitive impairments [screened by Mini-Mental Status Examination (MMSE) [42]: illiterate (uneducated) group ≤ 17points; primary school (years of education ≤ 6 years) group ≤ 20 points; middle school or higher (years of education > 6 years) group ≤ 24 points]. Conscious, stable physical condition and signed informed consent of patient.

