### Randomization and allocation

The random allocation sequence will be produced by an independent statistician via the PLAN sentences of the statistical software SAS9.1, who works in the Evidence-Based Center of the university and is not involved in the study. The eligible patients will be randomly and blindly allocated to the study groups (EG1, EG2, EG3, CG) to ensure internal validity of results according to 1:1:1:1(equal proportion rule). The random allocation sequence will be managed by a specified research assistant (RA) who is not involved in this trial and be concealed to the screeners and assessors until the last outcome assessment of the patient has been performed. The treating therapists (acupuncturist) will be notified of the allocation and arrange directly with the patient for the allocated treatment to be given. The eligible participants will be informed which group they are in by the project manager.

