### Data collection and management

Having sought consent, the demographic and baseline characteristic data in CRFs will be completed by a specific RA who is masked to treatment allocation and trained to administer questionnaires in a standardized way.

The data consists [55] of demographic details, review of medical history and medication, the lesion, affected side, handedness, cognitive function, time since stroke, stroke type and subtype, rehabilitation history (treatments until study start), details of current and cognitive treatment received within the previous 3 months and concomitant medications are recorded. Data will be obtained by direct questions to patients, from medical records, and from a relative or proxy.

Outcome measurement will be measured by the outcome assessors after the intervention. RAs will conduct quality control of data collection and be responsible for data entry. The PL will be responsible for initial data cleaning, identifying, coding, and conversion into the proper format for data analysis.

All forms must be dated and signed by the responsible investigator or one of his/her authorized staff members.

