### Statistical analysis

All allocated subjects will be analyzed with the available data, i.e. on the basis of the intention-to-treat (ITT). A significance level of 95% (two sided p-values alpha < 0.05) will be used. After examining the data for normality (Kolmogorov-Smirnov test) the outcome measures will be analyzed using ANOVA (assuming normal distribution) or Kruskal-Wallis (non-parametric). Demographic characteristics and other baseline values will be described using descriptive statistics for each group. Significant group interactions will be analyzed post-hoc. We will use the Bonferroni method to appropriately adjust the overall level of significance for multiple outcomes.

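### Time since stroke can range up to six months at entry and is recorded at baseline, but the stated analysis has no covariate, so any outcome variation linked to it stays in the error term: a modest, avoidable loss of precision

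*Protocol article*

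**What the plan says.** All references are to the Protocol article.

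- **Inclusion criteria**: entry is open to "patients (age between 18 and 75 years old) within six months after first-ever stroke". There is an upper limit and no lower one. The same section also requires "Conscious, stable physical condition and signed informed consent of patient", which restricts very early entry in practice but sets no time.
- **Participant and recruitment**: "Patients will be recruited as inpatients or from the outpatient therapy department of the rehabilitation hospital". Both settings feed the sample, so a spread of intervals since stroke is to be expected.
- **Data collection and management**: the baseline items include "time since stroke, stroke type and subtype, rehabilitation history (treatments until study start", so the variable will be in the database.
- **Randomization and allocation**: patients are allocated "to ensure internal validity of results according to 1:1:1:1(equal proportion rule". No stratification factor is named there or under Quality control.
- **Statistical analysis**: outcomes are tested with ANOVA, or with Kruskal-Wallis if not normal, and no covariate is named. The one stated use of baseline data is that "Demographic characteristics and other baseline values will be described using descriptive statistics for each group".

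**The concern.** Two patients with the same baseline MMSE, one a few weeks after stroke and one in the sixth month, are both eligible and both followed for 12 weeks. If their expected courses differ, the difference is predictable from a variable the trial already records. An analysis without that variable treats predictable variation as noise.

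This matters more here than in a two-arm trial. The first aim is synergy, which is a contrast of all four cell means, and its variance is twice that of a comparison of two arms. The planned acupuncture-alone effect is also small, at 3.7 - 2.7 = 1.0 MMSE point. What is at stake is the width of the confidence intervals, not the validity of the comparison.

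**Working it through.** **Inputs from the Sample size section.** Planning means for MMSE improvement: CG 2.7, EG1 5.9, EG2 3.7, EG3 6.0. SD 5.2, read here as the SD of the improvement. Two-sided alpha 0.05, power 90%, about 50 per group, 60 per group after allowing for dropout.

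**Inputs assumed.** Half the patients are early entrants. They gain d = 2 to 4 MMSE points more over 12 weeks than late entrants, equally in every arm. The documents give neither figure.

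**1. The plan's own figure.** The mean of the four means is 4.575. The sum of squared deviations is 3.516 + 1.756 + 0.766 + 2.031 = 8.0675. A one-way ANOVA with four groups and noncentrality n x 8.0675 / 5.2² needs n = 49 per group (power 90.3%), and n = 50 gives 91.0%. The stated 50 is reproduced. Nothing in the sample size is wrong on this point.

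**2. Variance linked to time since stroke.** A two-category variable split 50:50 with gap d contributes 0.25 x d² to the variance.
- d = 2: 1.00 of 27.04 = 3.7%. Residual SD = sqrt(26.04) = 5.10.
- d = 4: 4.00 of 27.04 = 14.8%. Residual SD = sqrt(23.04) = 4.80.

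Standard errors shrink by 1 - 5.10/5.2 = 1.9% to 1 - 4.80/5.2 = 7.7%.

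**3. Effect on the contrasts at 60 per arm.** The interaction standard error is SD x sqrt(4/60); the pairwise one is SD x sqrt(2/60). Power is Φ(|effect|/SE - 1.96) + Φ(-|effect|/SE - 1.96). The interaction implied by the planning means is 6 - 5.9 - 3.7 + 2.7 = -0.9.

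| | Unadjusted | d = 2 | d = 4 |
|---|---|---|---|
| SE, interaction | 1.34 | 1.32 | 1.24 |
| Power for -0.9 | 10.3% | 10.5% | 11.2% |
| SE, acupuncture vs control | 0.95 | 0.93 | 0.88 |
| Power for 1.0 | 18% | 19% | 21% |

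At the 50 evaluable per group of the plan, power for the interaction moves from 9.4% to between 9.6% and 10.2%.

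**4. Effect on the planned four-group test.** If the covariate explains 5% or 10% of the variance, power at 50 per group rises from 91.0% to 92.4% or 93.8%.

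**5. Chance imbalance is the same quantity, not an addition.** The SD of the imbalance in early share for the four-cell contrast is sqrt(4 x 0.25/60) = 0.129. Times 2 to 4 points this is 0.26 to 0.52. The unadjusted variance of the interaction is 1.3426² = 1.803. Subtracting 0.258² = 0.067 leaves 1.736, and subtracting 0.516² = 0.267 leaves 1.536. The square roots are 1.32 and 1.24, exactly the adjusted standard errors in step 3.

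**The case against.** **The choice of covariates belongs to the SAP.** Neither the SAP nor the full protocol is shown, and the article does not say that baseline values are used for description only. Both points are fair: the text states a descriptive use without excluding others. What remains is that the section is not silent. It commits to named tests as the analysis of the outcomes; as named they carry no covariate, and Kruskal-Wallis cannot take one.

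**A reader might infer that unstratified allocation biases the comparison, or that imbalance adds error beyond the plan.** The documents support neither. Randomisation keeps the contrasts unbiased, and step 5 shows that the imbalance is already inside the SD of 5.2 and so inside the planned error term.

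**A reader might take the control arm's planned gain of 2.7 points as spontaneous recovery.** The article attributes it to cited papers and preliminary data, not to any mechanism. Control patients receive medication, physiotherapy, occupational therapy and health education. The MMSE is also the screening test and is repeated at 4, 8 and 12 weeks, so practice and regression to the mean could contribute.

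**A reader might picture entry in the first days after stroke.** No minimum is set, but the requirement of stable condition, the exclusion of patients unable to follow instructions and the rehabilitation-hospital setting make that unlikely.

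**Other recorded variables could be chosen instead**, such as lesion or stroke type. That is true, and the article does not rank them. Time since stroke is a reasonable candidate because the entry window is wide relative to the 12-week follow-up, but its prognostic strength here is an assumption.

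**Conclusion.** The point holds as a matter of precision. The entry criterion allows a wide range of time since stroke, the variable is collected, and the analysis as written leaves it out. On the assumptions of a 50% early share and a 2 to 4 point gap, adjustment would remove 4 to 15% of the residual variance and shorten standard errors by 2 to 8%. If the gap is smaller, or if the baseline score already captures part of it, the gain is smaller.

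The trial is not invalidated, the sample-size figure stands, and adjustment does not solve the weak power for the interaction or for acupuncture alone. Those come from the size of the planned effects relative to n. The case for the change is that the gain, though modest, costs nothing.

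**What to change.** Before unblinding, prespecify a 2 x 2 factorial ANCOVA for MMSE with acupuncture, RehaCom and their interaction as factors, and with baseline MMSE and time since stroke (continuous) as covariates. Use the same form for MoCA and FIM with their own baseline scores. If a fallback for non-normal data is kept, it should be one that can carry the covariates, which Kruskal-Wallis cannot.

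Leave the allocation sequence as it is. Introducing strata during recruitment would mix two allocation schemes, and the model term does the work without it.

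The cost is a short addition to the analysis text. No new data are needed. The article reports recruitment as ongoing and keeps the group code closed until the analysis is complete, so the term can be fixed without knowledge of results. Added after unblinding, it would be open to challenge as post hoc.
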